#### 20.11c Post-program employment

We will use a logistic multivariate regression analysis to model post-program employment where the observation for post-program employment will be coded as binary: full-time (=1) and not full-time (=0). The interventions (Distress thermometer and MH&A) will be included as well as a variable for their interaction effect. We will also include time period (year-quarter) and an interaction term between the time period and each intervention (Distress thermometer and MH&A). Clustered robust standard errors will be used to account for cohort intra-cluster correlation. Post-regression analyses using *margins* command will be used to estimate difference in post-program employment between treatment groups.

### 20.12 Secondary

#### 20.12a Mental Health & Addictions support

We will use a 3-level hierarchical design to model the time difference to access MH&A support data. Level 1 observations are clustered within individual apprentices (Level 2) , which are nested within cohorts (Level 3). We will analyse the outcome data using multi-level, mixed-effects linear regression analysis with fixed effects estimated for the variance in the intercepts of both apprentice and cohort levels. The interventions (Distress thermometer and MH&A) will be included as well as a variable for their interaction effect. We will also include time period (year-quarter) and an interaction term between the time period and each intervention (Distress thermometer and MH&A). A sensitivity analysis will be conducted to compare this baseline model with an extended model that includes any baseline demographic or clinical variables that appear to be unbalanced at Level 1. The models will be compared using the likelihood-ratio comparison test for superiority. Post-regression analyses using *margins* command will be used to estimate the time difference to access MH&A support between treatment groups.

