## 5.2 Rationale

In previous iterations of the TDTP, the Case Manager and Program Director have developed relationships with many other external agencies and service providers to facilitate access for their clients. Most of these relationships have involved basic communication and referrals, and would be described as minimally active relationships (16). For some problems, however, such as mental health and drug and alcohol addictions, the Case Manager has experienced difficulty in timely access to healthcare services. These delays have had negative consequences for program attendance and completion ([name], Program Director, personal communication). The Program Director has indicated that a more cooperative and coordinated relationship (16) with these services might benefit their clients. To this end, Community Builders® is partnering with Mental Health & Addictions (MH&A) services at the Royal Victoria Regional Health Centre (RVRHC) to develop a fit-for-purpose referral and access process that will ensure appropriate and timely care for those at-risk apprentices. As part of this novel case management strategy, we will also introduce a remote self-reporting tool for distress that will be completed by apprentices and monitored by the Case Manager to pre-emptively identify apprentices at-risk of absenteeism or drop-out with the hope that early identification and intervention will be more effective than the usual case management approach. A real-world (pragmatic) randomised study is therefore needed to compare the effectiveness of this Intensive Case Management approach compared to the usual Brokered Case Management approach for apprentices enrolled in the TDTP. This study is needed to demonstrate the superior benefits of ICM on important outcomes such as improved skills training retention and completion and post-training employment in order to justify its implementation across other vocational training programs with at-risk youth.

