## 11.2 Mental health & addictions

When an apprentice has been identified as being in a high priority group due to a mental health or addictions stressor, the Case Manager will contact (by email or text message) the triage counsellor for the MH&A program intervention. After this initial contact, a standard referral form will be sent to the Case Manager at Community Builders to complete and return to the MH&A triage counsellor. The triage counsellor will review the referral form immediately and schedule an appointment with a MH&A healthcare provider. The timing of the appointment will be determined by the triage counsellor but will always occur within 24 to 48 hours of the referral. The triage counsellor will also determine the need for an in-person versus audio/video consultation.

For any apprentice identified as being at high risk for suicide, the triage counsellor will instruct the Case Manager to take the apprentice to the RVRHC Emergency Department where they will be assessed by the MH&A crisis team.

For any apprentice identified as being in either drug withdrawal or relapse, the triage counsellor will schedule an appointment with healthcare providers at the RVRHC Rapid Access Addiction Medical clinic. The appointment will always occur within 24 to 48 hours of the referral.

For any apprentice that requires treatment or admission to a MH&A program that limits their availability to complete the TDTP, they will be withdrawn from their cohort and enrolled in a subsequent TDTP cohort after resolution of their health-related issues. For all other apprentices who access MH&A services, they will continue to attend their TDTP and continue to be supported according to their allocated case management model.

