## 12.2 Secondary outcome measures

### 12.21 Mental Health & Addictions support

Difference in time to access mental health & addiction services, where ***time to access is defined as the difference (hours) between the date of referral from the Case Manager to the date of the MH&A appointment.***

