### 18.13 Study-specific data

| Data | Description | Data type |
| --- | --- | --- |
| **Cluster criteria** |  |  |
| City | Barrie vs Sudbury | Categorical |
| Enrollment | Quarter-year  Quarter (Q):  Q1=January 1 – March 31  Q2=April 1 – June 30  Q3=July 1 – September 30  Q4=October 1 – December 31 | Categorical |
| **Primary Outcomes** |  |  |
| Program completion | Yes | Categorical |
|  | No |  |
| Employment (full-time at 24 months) |  | Categorical |
| Self-report | Yes | Categorical |
|  | Employer verified |  |
|  | Employer not verified |  |
|  | No |  |
| **Secondary Outcomes** |  |  |
| Date/Time |  | Continuous |
| Mental health consult | ddmmyy:hh |  |
| Addictions consult |  |  |
| TDTP Satisfaction Survey | National Centre for Vocational Education Research Student Outcomes Survey (21) | Categorical |
| Distress Thermometer |  |  |
| Acceptability survey | Section 12.25 | Categorical |
| Feasibility survey | Section 12.26 | Categorical |

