All study-specific data that is survey-based (Section 18.13 and 18.13a) will be completed by apprentices during orientation or after the completion of the TDTP. Secure links for each of the surveys will be sent by email to each apprentice. All survey responses will be stored in REDCap using the previously assigned unique identifier. Study-specific data related to clinical outcomes will be extracted by study personnel from the electronic medical record system (dates and times of Mental Health and/or Addictions healthcare visits) and stored in REDCap. All other study-specific outcome data related to program completion and employment (Section 18.13) will be collected by study personnel who will enter the data in REDCap.

All study data will be archived in REDCap for 10 years and subsequently permanently destroyed.

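### Time to MH&A access is fixed as a linear model on a duration that referrals without an appointment do not have, so long usual-care waits are likely to drop out

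*Protocol*

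**What the plan says.** Protocol section 12.21 defines the outcome: "time to access is defined as the difference (hours) between the date of referral from the Case Manager to the date of the MH&A appointment". It gives no time window, although sections 12.11, 12.12 and 12.22 each state 12 weeks for their outcomes.

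Section 20.12a fixes the model: "We will analyse the outcome data using multi-level, mixed-effects linear regression analysis". It has three levels, with observations nested in apprentices and apprentices in cohorts. Post-regression margins "will be used to estimate the time difference to access MH&A support between treatment groups".

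The data behind the outcome are dates of contact. The table in section 18.13 lists "Mental health consult | ddmmyy:hh" and an addictions counterpart. Section 19 has study personnel extract from the medical record the "dates and times of Mental Health and/or Addictions healthcare visits) and stored in REDCap". Neither section lists a not-seen status or a censoring date. The timeline in section 13 marks the outcome at T2 (days 61-70), directly after the programme column (days 1-60, M-F).

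On the expected waits, section 11.2 says of the appointment with the service that it "will always occur within 24 to 48 hours of the referral". Section 5.2 says that for mental health and addictions problems "the Case Manager has experienced difficulty in timely access to healthcare services", and that these delays harmed attendance and completion.

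**The concern.** The outcome exists only once an appointment exists. A referral still without one at the cut-off is known to have waited at least that long, but a linear model has no way to use that information, so the row is lost. No section assigns such a referral a value or a censoring time. By contrast, section 20.12b does carry follow-up time into the model for healthcare days, as an exposure period.

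The loss is unlikely to be even across groups. With the service, a wait of one to two days is almost always complete before any plausible cut-off. Under usual case management, the protocol's own rationale is that waits are long. It also says that delay harms completion, so people may leave while waiting. The discarded referrals would then be mostly the longest usual-care waits, and the estimated benefit of the service would shrink as usual access worsens. Time to access is what the service is built to shorten, and it is named in secondary objectives 1 and 5.

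**Working it through.** The protocol gives no sample size, effect size, SD or usual-care wait for this outcome, so there is no stated figure to reproduce.

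**Inputs from the protocol**
- Programme length: 12 weeks = 84 calendar days (section 5.15).
- Wait with the service: 24 to 48 hours (section 11.2), midpoint 36 hours.
- Assessment: T2, days 61-70 (section 13). If days are counted Monday to Friday, as the M-F label suggests, 60 days is 12 weeks and day 70 falls two weeks later, at calendar day 84 + 14 = 98.

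**Assumptions, not in the protocol**
- Referrals are spread evenly over the 84 days.
- Usual-care waits are exponential with mean m = 7, 14 or 30 days.
- Records close at day 84 or day 98.

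**Formulas.** Time available from referral to closure is uniform on (a, b), with (a, b) = (0, 84) or (14, 98).
- Share with no appointment: u = (m/84) × (e^(−a/m) − e^(−b/m)).
- Mean among observed appointments: [m − J/84] / (1 − u), where J = m(a + 2m)e^(−a/m) − m(b + 2m)e^(−b/m).

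**Example, m = 14, closure at day 84**
- u = (14/84)(1 − e^(−6)) = 0.1663.
- J/84 = (392 − 14 × 112 × 0.00248)/84 = 4.62.
- Observed mean = (14 − 4.62)/(1 − 0.1663) = 11.25 days, and 11.25/14 = 80%.
- Difference from 36 hours: true 14 × 24 − 36 = 300 h; observed 11.25 × 24 − 36 = 234 h.

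| Closure | True mean (days) | No appointment | Observed mean (days) | Observed / true | True vs observed difference (h) |
|---|---|---|---|---|---|
| Day 84 | 7 | 8.3% | 6.4 | 91% | 132 vs 117 |
| Day 84 | 14 | 16.6% | 11.2 | 80% | 300 vs 234 |
| Day 84 | 30 | 33.5% | 17.6 | 59% | 684 vs 386 |
| Day 98 | 7 | 1.1% | 6.8 | 97% | 132 vs 126 |
| Day 98 | 14 | 6.1% | 12.2 | 87% | 300 vs 257 |
| Day 98 | 30 | 21.0% | 19.7 | 66% | 684 vs 437 |

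A simulation of 2,000,000 referrals per case agrees with these figures to rounding.

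**Checks on the direction**
- *Service group.* With waits uniform between 24 and 48 hours and closure at day 84, 1.8% are unseen and the observed mean is 36.0 h, so there is essentially no bias on that side.
- *Short usual-care waits.* With m = 3 and closure at day 84, the observed mean is 96% of the truth.
- *Non-attendance unrelated to the wait.* With 10% or 30% of referrals removed at random and m = 14, the mean stays at 14.0 days.
- *Longer follow-up.* With records read 90 days after programme end (a = 90, b = 174), 0.03% are unseen at m = 14 and 1.7% at m = 30. Observed means are then 99.8% and 94% of the truth.
- *Keeping unseen referrals as censored.* Total time at risk divided by appointments observed, with closure at day 84, returns 7.0, 14.0 and 29.9 days.

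**The case against.** The strongest reply has five parts.

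- **When the interval ends.** A reader might infer that only kept appointments count. Section 12.21 says appointment, and section 11.2 uses that word for something the triage counsellor schedules, so a booked but unattended referral could still have a value. The consult and visit wording in sections 18.13 and 19 points the other way. This stands: the text supports either reading. A referral with neither a booking nor a visit is lost on both.
- **Cut-off and usual-care waits.** Both are assumed. Section 5.2 gives no duration and names no site for the past difficulty, and no section describes waits in Sudbury, where the comparator without the service sits. This stands, and it limits the size, not the mechanism. Mean waits of 60 days or more would give far larger losses, but nothing in the protocol anchors them.
- **Direction.** A reader might infer that bias toward no difference is certain. It is not: it requires that lack of an appointment be related to length of wait. The protocol's contrast between 24-48 hours and delayed access makes that the expected case, but does not prove it.
- **Skewness and unequal variance.** These mainly affect standard errors, not the mean difference. That is fair, and the point does not rest on them.
- **Rules for absent values belong in the SAP.** That is true of detail. Here, though, the protocol itself fixes both an outcome that needs an appointment date and a model that cannot use a referral without one.

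**Conclusion.** The point holds as a weakness in a fixed analysis of a secondary outcome. Referrals without an appointment by the cut-off leave the model, and the protocol's own account makes long usual-care waits the likely ones to go, which would understate the benefit of the service.

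Under the stated assumptions, the usual-care mean is recovered at 59% to 91% for closure at day 84 and 66% to 97% for closure at day 98, over mean waits of 7 to 30 days. Those ranges illustrate the mechanism; they are not estimates for this trial. The bias nearly disappears with short waits, with much longer follow-up, or if non-attendance is unrelated to the wait. Even the attenuated differences in the table remain large in hours, and the primary outcomes are untouched. The change is worth making, but the trial's main conclusions do not depend on it.

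**What to change.** In sections 12.21, 18.13 and 20.12a:

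1. Define whether the interval ends at the scheduled appointment or at the attended visit, and use one term throughout.
2. Keep every referral in the analysis, including repeat referrals within an apprentice. Record a not-seen status and a censoring date for each.
3. State the censoring date, and follow each referral to it whether or not the apprentice is still in the programme.
4. Replace the linear model with a comparison of restricted mean time to appointment up to a stated horizon, with Kaplan-Meier curves and cohort-clustered standard errors. A proportional-hazards model is a poor first choice, because waits held to 24-48 hours against long, variable waits are unlikely to have proportional hazards.
5. Report the proportion of all referrals seen within 48 hours and by programme end, with unseen referrals in the denominator.

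The cost is slightly more analysis work, one extra status field, and a restricted mean in place of a simple mean difference in hours. No extra participants or visits are needed. Not-seen status is best captured prospectively, so the change should be made before enrolment starts.

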#### 20.12b Healthcare utilization

We will model the days of healthcare utilization as count data, with the period of follow-up while alive during the study period as the exposure period. We will analyse the data using a Poisson multivariate regression model. The interventions (Distress thermometer and MH&A) will be included as well as a variable for their interaction effect. We will also include time period (year-quarter) and an interaction term between the time period and each intervention (Distress thermometer and MH&A). Clustered robust standard errors will be used to account for clustering of data within apprentices.

#### 20.12c Apprentice satisfaction

We will use linear multivariate regression analysis to model the differences in mean scores for each domain (3 major themes and summary question) of the National Centre for Vocational Education Research Student Outcomes Satisfaction Survey. The interventions (Distress thermometer and MH&A) will be included as well as a variable for their interaction effect. We will also include time period (year-quarter) and an interaction term between the time period and each intervention (Distress thermometer and MH&A).

#### 20.12d Case management utilization

We will use linear multivariate regression analysis to model the mean difference in cumulative hours spent on case management by the Training Program Coordinator. The interventions (Distress thermometer and MH&A) will be included as well as a variable for their interaction effect. We will also include time period (year-quarter) and an interaction term between the time period and each intervention (Distress thermometer and MH&A).

#### 20.12e Acceptability and feasibility of self-report tool

We will use linear multivariate regression analysis to model the difference in mean scores for each question in both the acceptability and feasibility scales. The interventions (Distress thermometer and MH&A) will be included as well as a variable for their interaction effect. We will also include time period (year-quarter) and an interaction term between the time period and each intervention (Distress thermometer and MH&A).

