## 7.2 Secondary

1) To compare the effect ICM^10^ and ICM^01^ versus BCM on time to access mental health & addiction services

2) To compare the effect ICM^10^ and ICM^01^ versus BCM on utilization of healthcare visits

3) To compare the effect ICM^10^ and ICM^01^ versus BCM on National Centre for Vocational Education Research Student Outcomes Survey Satisfaction scores

4) To compare the effect ICM^10^ and ICM^01^ versus BCM on mean hours spent on case management by the Case Manager

5) To compare the effect of ICM^11^ versus ICM^10^ and ICM^01^ on time to access mental health & addiction services

6) To compare the effect of ICM^11^ versus ICM^10^ and ICM^01^ on utilization of healthcare visits

7) To compare the effect of ICM^11^ versus ICM^10^ and ICM^01^ on National Centre for Vocational Education Research Student Outcomes Survey Satisfaction scores

8) To compare the effect of ICM^11^ versus ICM^10^ and ICM^01^ on mean hours spent on case management by the Case Manager

9) To measure acceptability of using self-report tool for distress by apprentices and Case Manager

10) To measure feasibility of using self-report tool for distress by apprentices and Case Manager

11) To measure compliance of using self-report tool for distress by apprentices

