
## 11.12 Web-based, self-report tool for distress

The Distress Thermometer screening tool will be integrated into a web-based, self-reporting tool that apprentices will be asked to complete on a daily basis (Monday to Thursday) prior to attending their in-class or on-site session for the 12-week duration of the TDTP. Apprentices whose cohorts are randomized to either ICM^10^ or ICM^11^ will be provided with a tablet computer to access the Distress Thermometer screening tool. Apprentices will login using a unique username and password system. The Case Manager will have immediate access to each apprentice’s daily distress score, including all of their previous scores. The scores will be prioritized according to the following criteria:

1. High Priority Distress score ≥ 4 + Answer “Yes” to last question, or

Answer “Yes” to last question

A referral may also be made if the apprentice’s distress level is escalating defined as a change of ≥ 2 on the distress score from previous day.

2. Medium Priority Distress score≥4 + Answer “No” to last question

3. Low Priority Distress score ≤3 + Answer “No” to last question

The Case Manager will immediately contact (by phone) all apprentices in the high priority group to coordinate a care management plan personalized for their identified stressor(s). For those apprentices identified as medium priority, a one-on-one in-person meeting with the Case Manager will be scheduled to occur within 48 business hours in order to coordinate a personalized care management plan for their identified stressor(s). For those apprentices identified as low priority, a quick check-in with the Case Manager will take place within the work week to determine if any special care management issues need to be addressed. The care management plan is not dictated by the study but is left to the discretion of the Case Manager and apprentice. The care management plan will be documented within the web-based, self-report tool.

For those apprentices who do not compete a daily assessment by 8 am, the Case Manager will reach out by email/phone immediately to the apprentice to enquire about their status. For those apprentices experiencing severe distress, they have the option of directly contacting (email/phone) the Case Manager instead of completing the Distress Thermometer screening tool.

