## 11.3 Compliance

To promote study enrollment and adherence with study-related tasks, each enrolled apprentice will be provided with a tablet computer for the duration of the TDTP to support their participation and promote adherence to daily screening with the Distress Thermometer self-reporting tool. Apprentices who complete ≥ 90% of their daily Distress Thermometer screens will receive $50 for their time and effort and be enrolled in a draw for 5 tablet computers. The Apprentices enrolled in ICM^10^ and ICM^11^ do have the option of not completing the Distress Thermometer screening tool. These apprentices will be asked to relate the reason for each episode of non-compliance from a fixed list available in the self-report tool. Apprentices who choose not to complete the Distress Thermometer screening tool but document the reason will be considered to be compliant for that episode.

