### 12.25 Acceptability of self-report tool

To measure the acceptability of using the Distress Thermometer screening tool by apprentices and the Training Program Coordinator, where ***acceptability is measured using a 2-item questionnaire.*** The 2-item questionnaire was developed to measure acceptability of the Distress Thermometer tool among different user groups (22). The 2-items are:

1. Rate the degree of difficulty you encountered in using (monitoring) the Distress Thermometer screening tool.

The response options are: *Very easy (score=1); Somewhat easy; Somewhat hard; Very hard (score=4)*

2. To what extent did completing (monitoring) the Distress Thermometer screening tool bother you?

The response options are: *Didn’t bother me at all (score=1); Bothered me a little bit; Bothered me a lot (score=3)*

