### 12.26 Feasibility of self-report tool

To measure the feasibility of using the Distress Thermometer screening tool by apprentices and the Training Program Coordinator, where ***feasibility is measured using a 1-item questionnaire.*** The 1-item questionnaire was developed to measure feasibility of the Distress Thermometer tool among different user groups (22). The 1-item questionnaire is:

1. How feasible was it to use (monitor) the Distress Thermometer on a daily basis?

The response options are: *Very feasible (score=1); Somewhat feasible; Somewhat infeasible; Very infeasible (score=4)*

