## 16.3 Implementation

Cohort randomization will be requested by the TDTP Training Program Coordinator from the independent study coordinator (Section 16.2) 1 week prior to that cohort’s TDTP start date by calling a centralized study telephone number. The study coordinator will access the random allocation sequence through REDCap®, and then inform the Training Program Coordinator of the allocation for the cohort. The Training Program Coordinator will provide this allocation information to the TDTP students. Informed consent from each interested TDTP student in the randomized cohorts ICM^1x^ will then be obtained by *TeachMeToBuild* study personnel (Section 15).

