#### 20.12f Compliance of self-report tool

We will use linear multivariate regression analysis to model the difference in mean compliance rates for the Distress Thermometer self-report tool. The interventions (Distress thermometer and MH&A) will be included as well as a variable for their interaction effect. We will also include time period (year-quarter) and an interaction term between the time period and each intervention (Distress thermometer and MH&A).

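### The acceptability, feasibility and compliance models include tool terms that cannot be estimated, because only tool cohorts have these data; what remains is a site contrast, whereas the objectives ask for a level

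*Protocol*

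**What the plan says.** Section 7.2 words the first eight secondary objectives as comparisons between case management models. Objectives 9 to 11 are worded differently. The ninth reads "To measure acceptability of using self-report tool for distress by apprentices and Case Manager", and the tenth and eleventh do the same for feasibility and for compliance by apprentices. The registration data set in section 1.1 follows the same split: these three outcomes are listed by name, whereas the other secondary outcomes are listed as differences.

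Section 20.12e plans linear regression of a difference in mean scores for each question and adds: "The interventions (Distress thermometer and MH&A) will be included as well as a variable for their interaction effect". It then adds year-quarter and an interaction of year-quarter with each intervention. Section 20.12f uses the same terms "to model the difference in mean compliance rates for the Distress Thermometer self-report tool".

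The tool is given to one half of the factorial only:

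- Section 11.12: "Apprentices whose cohorts are randomized to either ICM^10^ or ICM^11^ will be provided with a tablet computer to access the Distress Thermometer screening tool".
- Section 11.3: "The Apprentices enrolled in ICM^10^ and ICM^11^ do have the option of not completing the Distress Thermometer screening tool".
- Section 16.3: "Informed consent from each interested TDTP student in the randomized cohorts ICM^1x^ will then be obtained by" the study personnel.

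The items presuppose use of the tool. Section 12.25 asks "Rate the degree of difficulty you encountered in using (monitoring) the Distress Thermometer screening tool", and section 12.26 asks "How feasible was it to use (monitor) the Distress Thermometer on a daily basis". Section 12.27 defines compliance as completed daily screens divided by programme days.

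**The concern.** The sentence that specifies the model is the one used in sections 20.12c and 20.12d for satisfaction and case management hours, outcomes that can be observed in all four arms. Here there is no untreated half to compare with. A control apprentice has no screens to complete and no experience of the tool to rate.

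Two things are at stake. First, the model cannot be fitted as written. Software would drop terms, and which ones it drops depends on the package and the order of entry, so a surviving coefficient could carry the label MH&A or the label interaction for the same quantity. Second, the one contrast that survives is not an objective and is confounded with site, while the quantity that objectives 9 to 11 ask for is not named as an estimate in either section.

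**Working it through.** The protocol gives no sample size, power or other figure for these three outcomes, so there is no stated number to reproduce. The check is whether the specified terms can be estimated.

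**Inputs.** T = 1 for a tool cohort (section 11.12). M = 1 for MH&A, which section 8 makes available at Barrie only. Q is the number of year-quarters in which cohorts start. The protocol does not give Q, so 2, 4, 8 and 12 are assumed. Every arm is assumed to have a cohort in every quarter; gaps would only lower the rank further.

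**Model in 20.12e and 20.12f.**

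E(Y) = b0 + bT·T + bM·M + bTM·T·M + Σ g_q + Σ d_q·T + Σ h_q·M, where each sum runs over the Q−1 quarter indicators.

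Parameters: 4 + 3(Q−1) = 3Q+1.

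**Restrict to cohorts with data (T = 1).**

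E(Y) = (b0 + bT) + (bM + bTM)·M + Σ (g_q + d_q) + Σ h_q·M

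The data determine only the bracketed sums and the h_q:

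- b0 and bT appear only together: one parameter lost.
- bM and bTM appear only together: one lost.
- g_q and d_q appear only together: Q−1 lost.

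Total lost: 1 + 1 + (Q−1) = Q+1. Rank: (3Q+1) − (Q+1) = 2Q.

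**Numerical rank of the design matrix.**

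| Q (assumed) | Parameters | Rank, all four arms | Rank, tool cohorts | Aliased |
| --- | --- | --- | --- | --- |
| 2 | 7 | 7 | 4 | 3 |
| 4 | 13 | 13 | 8 | 5 |
| 8 | 25 | 25 | 16 | 9 |
| 12 | 37 | 37 | 24 | 13 |

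The model is sound for outcomes seen in all four arms and rank-deficient for these three. In tool cohorts the separate coefficients bT, bM and bTM each fail the estimability test. The sum bM + bTM passes. That sum is ICM11 versus ICM10, and because MH&A x quarter is also in the model it refers to the reference quarter.

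**What that contrast is.** Among tool cohorts, M = 1 means Barrie and M = 0 means Sudbury. Randomisation assigns the tool within site; it does not assign site. The contrast is therefore a non-randomised site difference.

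**After deleting the tool terms.** Intercept, MH&A (site), quarter and MH&A x quarter give 1 + 1 + (Q−1) + (Q−1) = 2Q parameters with rank 2Q. The model is full rank and can deliver mean levels.

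**The case against.** **The comparison rule already allows for this.** Section 20.1 limits comparison with BCM to analyses where it applies. That excuses the absence of a BCM comparison here. It does not cure sections 20.12e and 20.12f, which write the tool terms in explicitly.

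**Software will drop the aliased terms.** It will, and marginal means from the reduced fit would give the levels. But neither section plans them: post-regression margins are named for the primary outcomes and for time to access, not here. Both sections name a difference as the target.

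**Control cohorts also touch the system.** Section 11.3 promises a tablet to each enrolled apprentice, and sections 12.24 and 18.12 have the coordinator log hours and attendance in the tool. This gives control apprentices no daily screens and nothing to rate. Coding their compliance as zero would make a tool effect true by construction.

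**Details belong in the SAP.** Item-level tables and the exact interval method may well be left there. A model stated in the protocol that cannot be estimated is a different matter from an omitted detail.

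A reader might also infer three stronger points that the protocol does not support:

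- *That clustering is ignored.* Sections 20.12e and 20.12f name no technique, but section 20.1 requires all inferential and descriptive analyses to account for apprentice and cohort clustering. No claim about understated standard errors follows.
- *That nothing in the protocol could yield a level.* Section 20.1 refers to descriptive analyses, and sections 12.25 to 12.27 define scores and a ratio that can be summarised. The fair point is that the sections devoted to these outcomes name only a difference.
- *That coordinator responses are too few to model.* The protocol does not say how many coordinators or Case Managers answer, or how often; section 5.15 describes a Case Manager for each cohort. It can be said only that section 20.12e does not separate their answers from the apprentices'.

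**Conclusion.** The point holds for both sections. As written, Q+1 of 3Q+1 parameters are aliased, and no separate tool, MH&A or interaction coefficient can be estimated for acceptability, feasibility or compliance. The only estimable contrast among these is ICM11 versus ICM10, which is confounded with site and answers none of objectives 9 to 11.

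This rests on the protocol's statements that only ICM10 and ICM11 cohorts use the tool and on the wording of the items and the compliance ratio. The parameter counts depend on the assumed Q; the aliasing does not.

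The reach is limited to three of eleven secondary objectives. A reader might infer that the same flaw affects the primary analyses, since they share the sentence on interventions and interaction. It does not: with outcomes in all four arms the same set of terms has full rank. The confounding of MH&A with site runs through the whole design and is not a separate fault of these two sections.

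**What to change.** Rewrite sections 20.12e and 20.12f as follows:

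- Restrict the analysis to ICM10 and ICM11 cohorts.
- Delete the tool term, the tool x MH&A interaction and the tool x year-quarter interaction.
- Name the estimate as the level: the mean and category percentages for each acceptability and feasibility item, and mean compliance, each with a 95% confidence interval that accounts for cohort clustering, in line with section 20.1.
- Report apprentice and coordinator responses separately.
- If a Barrie versus Sudbury difference is shown, label it descriptive and confounded with site.

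This is a change of wording. It needs no new data and less modelling than now planned, and it lets objectives 9 to 11 be answered.
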